### Secondary and other endpoints

The secondary and other endpoints are as follows.
FMD at 0, 3, 6, 9, 12, 15, 18, and 21 months after treatment initiation.Aortic calcification index (ACI) at 0, 12, and 24 months after treatment initiation.ESC count in the blood at 0, 3, 6, 9, 12, 15, 18, 21, and 24 months after treatment initiation.Serum levels of vascular endothelial growth factor (VEGF), MCSF, 8-hydroxydeoxyguanosine (OHdG), and malondialdehyde (MDA) at 0, 3, 6, 9, 12, 15, 18, 21, and 24 months after treatment initiation.Incidence of cardiovascular diseases, cerebrovascular diseases, and stenosis of blood access during the 24 months.Adverse events of oral intake of RJ.

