### ESC count

The ESC count will be determined using flow cytometry as previously reported [32]. Fresh peripheral blood mononuclear cells will be obtained by density gradient centrifugation, and cell counting will be performed immediately. The cells will be stained with the following antibodies: Brilliant Violet (BV) 421 mouse anti-human CD34 (IgG1, к), phycoerythrin (PE) CD133 (clone W6B3C1), and Alexa Fluor 637 mouse anti-human CD309 (VEGF-2) antibody. The following isotype control antibodies will be used: BV 421 mouse IgG1, к, PE mouse IgG1, к (clone MOPC-21), and Alexa Fluor (clone MOPC-21) antibodies. After surface staining for 30 min at 4 °C in the dark, the cells will be washed with phosphate-buffered saline solution. Surface-stained cells will be then subjected to fluorescence-activated cell sorting (FACS) using a BD LSRFortessa^TM^ flow cytometer. The ESC frequency will be defined as the number of cells per 10^6^ events for each sample. Based on the surface expression of CD34, CD133, and CD309, ESCs will be determined by flow cytometry and differentiated into four subpopulations, namely CD34^+^, CD34^+^CD133^+^, CD34^+-^CD309^+^, and CD34^+^CD133^+^CD309^+^ cells. These four cell subpopulations will be counted as ESCs as described previously [32].

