### Statistical analyses

The results of all examinations will be expressed as mean ± SD. To clarify the primary endpoint, the changes in the rates of FMD after treatment for 24 months (FMD for 24 months/baseline) will be compared between the RJ and placebo groups using the Student’s *t* test. Non-adherence and missing data will not be used in this analysis. A similar analysis will be performed to compare the changes in FMD at 6, 12, and 18 months between the two groups. For this analysis, missing data will be used according to the period of RJ administration. Other variables and data will be analyzed similarly at 6, 12, 18, and 24 months. There is no plan for any additional analyses. Permitted investigators (KO, YM, TM, KM) will have access to these interim results.

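### The single rule for all secondary endpoints (ratio to baseline, t test, at 6, 12, 18 and 24 months) cannot be applied to events or to ACI at 6 and 18 months, suits ESC and serum markers poorly, and leaves four visits without a planned comparison

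*Protocol article*

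**What the plan says.** All the analysis text is in the Statistical analyses section of the protocol article.

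- **Measure and test.** The main analysis is worded as follows: "the changes in the rates of FMD after treatment for 24 months (FMD for 24 months/baseline) will be compared between the RJ and placebo groups". The test is Student's t.
- **FMD at other times.** "A similar analysis will be performed to compare the changes in FMD at 6, 12, and 18 months between the two groups".
- **Everything else.** "Other variables and data will be analyzed similarly at 6, 12, 18, and 24 months".
- **Closing statements.** All examinations are summarised as mean and SD, and no analyses beyond these are planned. No other test is named anywhere in the article.

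The Secondary and other endpoints section lists what the rule has to cover:

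- endothelial function, listed as "FMD at 0, 3, 6, 9, 12, 15, 18, and 21 months after treatment initiation"
- calcification, on a sparser schedule: "Aortic calcification index (ACI) at 0, 12, and 24 months after treatment initiation"
- every 3 months from 0 to 24, ESC count and four serum markers (VEGF, MCSF, 8-OHdG, MDA)
- clinical events, listed as "Incidence of cardiovascular diseases, cerebrovascular diseases, and stenosis of blood access during the 24 months"
- safety, through adverse events

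The section defining the clinical events describes ischemic heart disease, arrhythmia and access stenosis as new-onset.

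**The concern.** One recipe written for a continuous measurement with a baseline is extended to endpoints of quite different kinds and on different schedules. For some of them the recipe has no input. For others it has an input but is a poor choice.

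The events are the clinical outcomes that motivate the trial, and adverse events are its safety endpoint. If the written rule cannot be followed, the analysts must pick a method later. The article lets named investigators see the interim results, so that choice could be made after data have been seen. Settling the methods now removes the doubt.

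**Working it through.** The plan gives no figure on this point to reproduce. The check is a comparison of two schedules, a test of whether the ratio exists for each endpoint, and one illustration under stated assumptions.

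**1. Schedules side by side** (months after start)

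| Endpoint | Measured | Compared between arms | Compared but not measured | Measured but not compared |
|---|---|---|---|---|
| FMD | 3, 6, 9, 12, 15, 18, 21; 24 is primary | 6, 12, 18; 24 is primary | none | 3, 9, 15, 21 |
| ACI | 12, 24 | 6, 12, 18, 24 | 6, 18 | none |
| ESC count | 3, 6, … 24 | 6, 12, 18, 24 | none | 3, 9, 15, 21 |
| Serum markers | 3, 6, … 24 | 6, 12, 18, 24 | none | 3, 9, 15, 21 |

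For FMD, ESC and serum markers, 8 − 4 = 4 of the 8 post-baseline visits have no planned comparison.

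**2. Does value/baseline exist?**

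- *Clinical events.* Most are new-onset by definition, and all are counted over the 24 months after the start. Each patient has zero such events at baseline, so the ratio is undefined for everyone.
- *Adverse events.* These likewise have no pre-treatment value to divide by.
- *Unequal follow-up.* The Safety management section ends all examinations at withdrawal, and the Sample size section allows for about 20% incomplete data and for dropouts. Dropping the ratio and running a plain t test on event indicators would still ignore this.
- *ACI.* The ratio can be formed at 12 and 24 months. At 6 and 18 months there is no value.
- *ESC frequency and serum markers.* The ratio can be formed whenever the baseline is above zero. A small baseline then produces a large ratio, and a few such patients can dominate a mean and its SD.

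**3. What the ratio costs where it can be computed (illustration)**

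Assumptions, none from the documents except the group size:

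- a log-normal marker with log-SD *s*
- a correlation of 0.5 between baseline and follow-up logs
- 112 patients per arm (the article's figure before allowance for losses)
- two-sided 5% level
- a treatment effect of 0.3744 *s* on the log scale

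That effect gives a familiar reference point. With correlation 0.5, the variance of log(follow-up) − log(baseline) is 2*s*²(1 − 0.5) = *s*². A t test on log ratios therefore has a standardised difference of 0.3744 × √(112/2) = 2.80, and 2.80 − 1.96 = 0.84, which is 80% power.

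Simulated power, 1,000 runs for each row:

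| log-SD | t test on raw ratio | ANCOVA on logs | mean skewness of ratio |
|---|---|---|---|
| 0.5 | 76% | 91% | 1.7 |
| 0.8 | 65% | 88% | 3.0 |
| 1.0 | 61% | 91% | 4.0 |

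The ANCOVA column should not depend on *s*. Its residual SD is *s*√(1 − 0.25) = 0.866 *s*, so the standardised difference is (0.3744/0.866) × √56 = 3.24, or about 90% power. The spread from 88% to 91% is simulation error (standard error √(0.9 × 0.1/1000) ≈ 1 percentage point).

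**The case against.** The best defence is that this is a condensed article, that a fuller protocol exists, and that *similarly* may mean only that the arms will be compared. On that reading, event incidence over 24 months would naturally be compared as proportions. This has some force: nothing in the text shows that anyone intends to divide events by a baseline. But the article names the measure, the test and the time points, and excludes further analyses. Even the loose reading leaves ACI scheduled at two times when it is not measured. A simple comparison of proportions also needs complete follow-up, which the article does not expect.

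Comparing arms at four visits rather than eight is a legitimate way to limit the number of tests. That stands. The fault is only that the other visits are listed as endpoints without being called descriptive.

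A reader might infer four stronger points, which the documents do not support:

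- *ESCs are counted up to four times.* The four phenotypes look nested, and the ESC count section says "These four cell subpopulations will be counted as ESCs as described previously". It does not say that they are summed. They may be reported as four separate frequencies.
- *Many ESC ratios are undefined because the baseline is zero.* No ESC level is given. With an assumed Poisson count, the expected number of zero baselines among 270 patients, 270 × exp(−mean), is about 99 at a mean of 1, about 2 at a mean of 5 and practically none at 10. No figure can be claimed.
- *The ACI ratio is undefined for uncalcified aortas.* This needs no calcification in any slice, and no ACI distribution is given.
- *The 3-, 9-, 15- and 21-month data are never used.* They can still be tabulated as mean and SD.

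**Conclusion.** The point holds in a limited form.

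- *From the text alone:* the stated rule cannot be executed for clinical events or adverse events, nor for ACI at 6 and 18 months. No between-arm comparison is planned for FMD, ESC or serum markers at 3, 9, 15 and 21 months.
- *Resting on assumptions:* for ESC frequencies and serum markers the ratio is computable in most cases but unsuitable. Under the assumptions above, its power is 61–76% against about 90% for a baseline-adjusted log-scale analysis. The true loss depends on marker levels, spread and correlation, which the article does not give.

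It would be wrong to say that the ACI or ESC results as a whole cannot be computed. The effect is confined to secondary and other endpoints, and no sample size or power figure changes. It should still be corrected, because the present sentence leaves the clinical-event and safety analyses without a workable method.

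**What to change.** Replace the sentence that extends the FMD analysis to all other variables with:

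1. **Clinical events.** Time to first event compared between arms by Cox model or log-rank test in all randomised patients, censored at withdrawal and cause-specific with respect to death. Say that censoring at withdrawal is assumed to be unrelated to event risk.
2. **Adverse events.** Number and proportion of patients with an event, in each arm.
3. **ACI.** ANCOVA adjusted for baseline ACI, at 12 and 24 months only.
4. **ESC frequencies and VEGF, MCSF, 8-OHdG and MDA.** Log-scale analysis adjusted for baseline, preferably a mixed model over all 3-monthly visits. Report each ESC subpopulation separately, and say beforehand how zero or undetectable values enter the log scale.
5. **Visits at 3, 9, 15 and 21 months, including FMD.** Either bring them into the planned comparison or state that they are descriptive only.

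The cost is a revised paragraph and minor extra programming. No new data and no additional patients are needed.

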### Data collection and management

Patients will be identified by a specific number, which will be assigned by independent staff. All clinical data will be collected from patient records. All data and information about this trial will be protected by passwords, and two persons responsible for information control will be able to access the data. In addition, three independent investigators will check the data for accuracy. Data monitoring will be performed according to the research plan approved by the clinical research review board of Nagasaki University. In short, the data management committee consisting of the approved data and information managers in Nagasaki University Hospital who were independent of competing interests and sponsors will oversee the handling of data, including storing and sharing data, every 3 months. To promote participant retention and complete follow-up, information on patients’ conditions and the data will be totalized in the executive office in Nagasaki University Hospital every 3 months. Any outcome data will be collected and listed for participants who discontinue or deviate, at the time of the event. All individual data and biological specimens will be preserved at the Nagasaki University Hospital until analyses. There is no plan to use the residual samples.

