### Safety management

If serious adverse events (SAEs) that are speculated to be associated with oral RJ intake, RJ administration will be discontinued. In case of the existence of a causal relation between SAEs and RJ, this study will be terminated. Judgments about RJ-related SAEs will be made by medical investigators at each institute and will be reported to the ethics committee within 24 h and to the coordinate centers within 3–5 days (3 working days). If mild adverse events occur, RJ administration will be discontinued until recovery. In this study, changes in drug dose will not be permitted. On the other hand, RJ administration and all examinations will be terminated in case of participant withdrawal. In addition, the principal investigator (YM) must decide to terminate the trial even if one investigator suggests early termination because of SAEs.

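### Adverse events and 24-month vascular and access events are sent to one of two data rules that depend on adherence or exposure, without saying which; either can drop patients or events after product is stopped

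*Protocol article*

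**What the plan says.** Among the secondary and other endpoints, the protocol article lists "Adverse events of oral intake of RJ" and "Incidence of cardiovascular diseases, cerebrovascular diseases, and stenosis of blood access during the 24 months".

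The Statistical analyses section gives two data rules, each attached to an FMD analysis:

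- FMD at 24 months (primary): "Non-adherence and missing data will not be used in this analysis".
- FMD at 6, 12 and 18 months: "For this analysis, missing data will be used according to the period of RJ administration".

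The next sentence covers everything else: "Other variables and data will be analyzed similarly at 6, 12, 18, and 24 months". The one after it closes the plan: "There is no plan for any additional analyses".

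Two other sections bear on this. Safety management stops product after a serious adverse event thought to be related to it, and for milder events says "If mild adverse events occur, RJ administration will be discontinued until recovery". It also ends all examinations when a participant withdraws. Data collection and management says "Any outcome data will be collected and listed for participants who discontinue or deviate, at the time of the event".

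**The concern.** For safety and clinical events, the set of patients compared should not depend on whether they kept taking the product, because stopping can be a consequence of the event. Here adverse events lead to stopping under Safety management, and both data rules on offer depend on adherence or exposure. A comparison that leaves out patients or follow-up for that reason selects partly on its own outcome.

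At stake are the between-arm comparison of adverse events and that of cardiovascular, cerebrovascular and access events. The Background hypothesis names the first two of these event types as what royal jelly (RJ) should reduce. The choice of set also needs to be fixed before unblinding, since a set chosen afterwards would be open to challenge. The point does not concern the primary FMD test.

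**Working it through.** The plan states no figure for this point, so the main check is to follow each reading of the carry-over sentence.

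**Step 1. Scope.** Adverse events and vascular and access events are listed endpoints other than FMD. They fall within the other variables and data that the sentence names, and no separate analysis is planned for them.

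**Step 2. The readings.**

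| Reading of the sentence | Event that led to product stop | Events after product stop |
|---|---|---|
| 24-month rule applies | Can be left out, if the patient counts as non-adherent or missing | Can be left out with the patient |
| 6/12/18-month rule applies (taken to mean that data up to product stop are used) | Counted | Lost |
| Only the test and time points carry over | No data set stated | No data set stated |

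The second row conflicts with the endpoint definition. If product stops for good at month *k*, then 24 − *k* months of the 24-month incidence period are not counted. For a stop at month 8, as an example, that is 24 − 8 = 16 months.

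**Step 3. How many patients a rule could touch.** The Sample size section expects incomplete data in about 20% of patients, with 135 per arm. 0.20 × 135 = 27 per arm, or 54 of 270. This is an upper indication for the 24-month rule; the document does not say how many of these would be adverse event stops.

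**Step 4. Effect on an adverse event comparison under the 24-month rule.** The document gives no event risks, so these are assumptions. Let *p* be the true risk in an arm and *s* the share of affected patients who are excluded, taken as equal in both arms. The observed risk is

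*p*(1 − *s*) / (1 − *ps*).

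For RJ 20% and placebo 10%, the expected numbers affected are 27.0 and 13.5 of 135.

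- *s* = 0: 20% v 10%, difference 10.0 points.
- *s* = 0.5: RJ 13.5/121.5 = 11.1%; placebo 6.75/128.25 = 5.3%; difference 5.8 points.
- *s* = 1: 0% v 0%.

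Other assumed risks at *s* = 0.5:

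- 10% v 5%: 5.3% v 2.6%, so the difference falls from 5.0 to 2.7 points.
- 30% v 20%: 17.6% v 11.1%, so the difference falls from 10.0 to 6.5 points.

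Under the 6/12/18-month rule, *s* = 0 for the triggering event and this loss does not arise; only later events go.

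**Step 5. Direction.** The formula shrinks a difference of either sign. With the arms reversed (RJ 10%, placebo 20%), a benefit of 10.0 points would appear as 5.8.

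**The case against.** The strongest case on the other side has four parts.

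1. *The exclusion rule is worded for the primary analysis only.* The rule nearest to the carry-over sentence is the other one, and it counts the event that led to stopping. This stands. A reader might infer that having an adverse event removes a patient from the safety comparison. The text allows that on one reading but does not settle it. The nearer rule still loses events after product stop.

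2. *The word similarly may refer only to the t test and the time points.* Means, SDs and a t test suit the calcification index, cell counts and serum markers better than incidences. If that was the intent, what remains is an unstated data set, which a condensed article may leave to the full protocol or the analysis plan and which would not be a point by itself. But the sentence as written covers all other variables and is followed by a statement that no further analyses are planned, so a reader who follows the text has only the two rules.

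3. *An adverse event stop need not mean exclusion.* A pause for a mild event is temporary, non-adherence is not defined, and outcome data are collected for participants who discontinue or deviate. All of this stands and limits how many patients would be lost. Collecting and listing data keeps the record; it does not say whether the patient enters the comparison.

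4. *A vascular event does not by itself stop product.* Safety management ties stopping to suspected relation to RJ, and a patient with an event during follow-up already has the outcome without a 24-month measurement. This also stands. Loss of vascular events arises through product stop or withdrawal for any reason, not through the event alone.

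**Conclusion.** The point holds in a limited form. The Statistical analyses section sends adverse events and 24-month vascular and access events to one of two rules that depend on adherence or exposure, does not say which, and closes off any other analysis. One rule can leave out patients stopped for an adverse event. The other drops events after product stop, against an endpoint that runs for 24 months.

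The size is not known. With assumed risks of 20% v 10% and equal exclusion in both arms, the difference goes from 10.0 to about 5.8 points if half of the affected patients are excluded.

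Two stronger conclusions are tempting, and the document supports neither. The first is that a real excess would vanish. For instance, 20/135 v 7/135 (Fisher p = 0.014) would become 0/115 v 0/128. That result is built in by assuming that every affected patient is excluded, which the document does not say. The second is that the bias always makes RJ look safe. For adverse events that is so only if RJ has the excess. For vascular events the direction depends on the unknown true effect: if RJ prevents events, as the Background hypothesises, the loss could hide a benefit.

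The endpoints are secondary and the remedy is wording. It should be fixed, but it does not put the primary analysis in doubt.

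**What to change.** Add to the Statistical analyses section that neither FMD data rule applies to safety or clinical events, and state:

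- **Adverse events:** compared by arm in all patients who took at least one dose of RJ or placebo, including those who stopped.
- **Cardiovascular, cerebrovascular and access events:** compared in all randomised patients as allocated, counted to 24 months or last contact, whether or not product was stopped.
- **Reporting:** numbers and percentages per arm, with a risk difference and 95% CI.

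This should be settled before unblinding. It changes no clinical rule and needs no extra patients, and no extra visits for data already recorded. According to the Follow-up section, patients attend 3–4 times a week for dialysis, so events after product stop can come from their records unless they have withdrawn. The small downside is that event effects are somewhat diluted by time off product.

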### Randomization

Randomization will be performed by an independent employee of Nagasaki University Hospital using the envelope method, and medical investigators at each institute will be responsible for allocating patients. In short, eligible patients will be randomly assigned in a 1:1 ratio using a computerized random number generator, and the allocation information will be placed in sealed envelopes. Each patient will be assigned a unique number to protect their personal information. The randomized list will be managed by only an independent data manager and will be concealed from all investigators and patients. All information regarding patient selection will remain confidential and unknown to all investigators, including outcome assessors and statisticians, until the completion of the trial. Emergent unblinding will not be possible in this trial.

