## Trial status

The protocol version is 1.0, 18 September 2020. Participant recruiting started in December 2020. The completion of recruitment is anticipated to be on 7 December 2022. The completion of the final follow-up is anticipated to be on 31 December 2024.

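### Between-group results at 6, 12 and 18 months are opened to four investigators as interim results, which conflicts with the promise that investigators and statisticians stay blind until the trial ends

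*Protocol article*

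**What the plan says.** Two sections of the protocol article bear directly on this point.

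**Statistical analyses.** After the primary t test at 24 months, the section adds: "A similar analysis will be performed to compare the changes in FMD at 6, 12, and 18 months between the two groups". It continues: "Other variables and data will be analyzed similarly at 6, 12, 18, and 24 months". It closes by listing four permitted investigators by initials, who "will have access to these interim results". The initials that the Safety management section gives for the principal investigator are among them.

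**Randomization.** "The randomized list will be managed by only an independent data manager and will be concealed from all investigators and patients". The next sentence reads: "All information regarding patient selection will remain confidential and unknown to all investigators, including outcome assessors and statisticians, until the completion of the trial". The section also rules out unblinding in an emergency.

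Three other sections give context. Study design describes the trial as double-blind and placebo-controlled. Safety management gives the principal investigator the decision to terminate when an investigator suggests it because of SAEs. Trial status says: "The completion of recruitment is anticipated to be on 7 December 2022", and puts the end of follow-up at 31 December 2024.

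**The concern.** A comparison of RJ with placebo cannot be run without knowing which participants form each group. The Randomization section withholds that from statisticians as well as investigators until the trial is over, and it exempts nobody. The Statistical analyses section nevertheless plans such comparisons at intermediate visits, calls the output interim, and hands it to investigators.

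If the access is used during the trial, people running a double-blind study would know the direction and size of the emerging difference while participants are still being treated and measured. One of them takes the SAE-related termination decision. Such knowledge can affect conduct in ways that no later analysis can detect or correct. No purpose is given for the early results: no decision in the article depends on them.

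**Working it through.** The plan states no figure to reproduce here. The check sets the passages side by side and then works out the timing.

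**Step 1: what the access covers.** *These interim results* refers back to the comparisons just described: FMD between the two groups at 6, 12 and 18 months, and other variables handled in the same way. They are by-arm comparisons. No sentence limits the access to pooled data or to groups under a coded label.

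**Step 2: what the blinding promise covers.** The sentence that keeps matters "unknown to all investigators, including outcome assessors and statisticians, until the completion of the trial" takes as its literal subject information on the selection of patients. It stands in the Randomization section, directly after the sentence that hides the list from all investigators, and it extends to assessors and statisticians. Read in place, it is a promise about allocation.

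**Step 3: is there an exception or a bridge?**
- The Randomization section names no exempt person and no unblinded statistician.
- Data collection and management lets two persons responsible for information control access the data. It does not say that they prepare or receive by-arm results, and it does not explain access for four investigators.
- The same section says that data are kept until analyses, without dating the analyses.

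No passage reconciles the two sections.

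**Step 4: timing.** The article gives no run date. Take the reading most favourable to the plan, in which each comparison waits until the whole cohort has reached the visit. Assume that the last participant starts treatment at the planned close of recruitment, 7 December 2022.

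| Visit | Last participant reaches it | Time left to 31 December 2024 |
|---|---|---|
| 6 months | 7 Dec 2022 + 6 months = about 7 June 2023 | almost 19 months |
| 12 months | 7 Dec 2022 + 12 months = about 7 December 2023 | almost 13 months |
| 18 months | 7 Dec 2022 + 18 months = about 7 June 2024 | almost 7 months |
| 24 months | 7 Dec 2022 + 24 months = about 7 December 2024 | about 3 weeks |

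A later treatment start would not change the conclusion: the last participant's 18-month visit always comes 24 − 18 = 6 months before that participant's primary measurement. So even on this reading, all three sets of results could exist before the primary endpoint is complete.

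**The case against.** **The comparisons may all be run at the end.** They are secondary time points of one FMD series, no run date is given, and *interim* could loosely mean intermediate visits. This stands as a possibility. But a restricted list of people allowed to see *interim* results has little purpose if nothing exists until the trial is over. If analysis at the end is what is meant, the access sentence misstates it and still needs correcting.

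**Group means do not reveal any one participant's arm.** This is true, and the independent data manager could in principle supply coded groups. The article states no such arrangement. What would certainly be disclosed is the comparative effect.

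A reader might also infer several stronger points that the article does not support:

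- *That the looks fall during recruitment and could steer enrolment.* Counting from the start of recruitment in December 2020 gives June 2021, December 2021 and June 2022. Those are the dates when only the first participants reach each visit, and the article describes no calendar-time look at partial data. Full-cohort looks come after recruitment closes.
- *That the type I error is inflated.* Four tests at 0.05 would give 1 − 0.95⁴ = 18.5% if independent, and about 16% to 13% at assumed correlations of 0.5 to 0.7. These figures apply only if any time point could carry the efficacy claim. The primary endpoint is fixed at 24 months, no efficacy stop is planned, and the only stated grounds for ending the trial are SAEs.
- *That the endpoint readings or other assessments are biased.* FMD is measured by a single investigator blinded to clinical details, who is not said to be on the access list. SAE causality is assessed by investigators at each institute, who are not identified with the four. Nobody is named as deciding on adherence.

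**Conclusion.** The conflict is in the current text and holds. One section keeps investigators and statisticians blind until the trial is complete. Another gives four investigators, including the principal investigator, what it calls interim results of comparisons between the arms. The two cannot both be followed if *interim* has its ordinary meaning.

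The conclusion rests on two readings: that the promise in the Randomization section concerns allocation, and that *interim* with a restricted list means access before the trial ends. Both are the natural readings, though neither is stated outright. On the latest plausible calendar, with each look waiting for the full cohort, the results would precede the planned end of follow-up by about 19, 13 and 7 months.

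The effect on the trial's results cannot be quantified. Bias through FMD readings, adherence or SAE assessments is a risk and is not demonstrated. The clearest exposure is that the person who takes the SAE-related termination decision would also see emerging effects by arm. The error rate of the primary test is not at issue.

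**What to change.** In Statistical analyses, delete the sentence giving investigators access to interim results. State instead that all comparisons between RJ and placebo, including those at 6, 12 and 18 months, are run once, after the last participant's 24-month visit and database lock, and that until then investigators see only pooled, blinded data. The Randomization section can then stand as it is, although replacing its reference to patient selection with treatment allocation would remove doubt about what is being kept confidential.

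The cost is a short amendment and the loss of an early look that serves no stated decision. No visit, measurement, treatment or sample size changes, and the intermediate comparisons are still reported.
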